### Aims and objectives

The aims of this study are to evaluate the effect of mecobalamin (vitamin B_12_) and to describe lived experiences of pain, health, suffering and well-being in women with diagnosed fibromyalgia.

The primary objective is to evaluate whether mecobalamin (vitamin B_12_), given as an intramuscular injection once a week for 12 weeks compared with placebo reduces pain sensitivity, that is, tolerance time (cold pressor test).

The secondary objective is to evaluate whether intramuscular mecobalamin (vitamin B_12_) compared with placebo reduces pain intensity and pressure pain threshold (Numerical Rating Scale (NRS) and pressure algometry), and increases activity level (questionnaire), quality of life (questionnaire) and perceived effect of a given drug (questionnaire). Furthermore, the ratings of expected effects of a given drug (NRS), the desire for pain relief (NRS) and estimated pain variability (NRS) are evaluated. Qualitative interviews that describe how women with fibromyalgia experience pain, health, suffering and well-being (interviews) will be conducted.

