### Measurements

At the first measurement opportunity, the trial manager and coexaminer 1 carefully follow inclusion and exclusion criteria. Oral information is given again, and consent is signed by the participant and by coexaminer 1. First, the participant answers two questionnaires (short-form McGill Pain Questionnaire (MPQ)^27^ and RAND-36 (RAND-36 Health-Related Quality of Life)),^28^ then stimulation tests (cold pressor test and pressure algometry)^29–33^ are performed followed by pain rating (NRS)^34^ immediately after 1 min and after 3 min. Finally, blood samples for cobalamin (vitamin B_12_), kidney, liver and heart markers are taken. The participant provides an information card about the study’s design, purpose, treatment options and contacts with telephone numbers. The participant is asked about her interest in an interview in connection with the final measurement opportunity. Coexaminer 2 assesses the blood samples and approves the final inclusion. If tests deviate from accepted reference values, the participant is excluded and encouraged to seek medical attention.

After the approved inclusion, an independent chief examiner performs the randomisation. The participant then receives intramuscular injections of the active substance or placebo, once a week for 12 weeks, given by a registered nurse. Before each injection, the participant answers questions in which he or she estimate his or her expected effects of a given drug, desire for pain relief and average pain intensity during the past week (NRS). The participant has the opportunity to postpone the visit for ±3 days, for example, in case of illness or travelling and may miss a maximum of two injections in order to follow per-protocol analysis. Even if the participant is not compliant with the study protocol, the participant may retain the treatment regime for the duration of the study and may be analysed in the main intention-to-treat analysis.

The second measurement takes place after 12 weeks of intervention and three questionnaires (MPQ, RAND-36 and Patient Global Impression of Change (PGIC))^35^ are filled out. The stimulation tests cold pressor test and pressure algometry are performed as well as blood sampling of cobalamin/p (vitamin B_12_). In cases of low cobalamin/p, the participant is encouraged to seek medical attention but is still included in the study.

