### Outcomes

The primary outcome is tolerance time, maximised to 3 min, which is tested using the cold pressor test.

The secondary outcomes are

Pain experience measured by a pressure algometry test performed on the shoulder, hip, knee and elbow.Possible pain change measured by a pressure algometry test performed on the shoulder, hip, knee and elbow.Subjective experience of pain measured using NRS of 0–10, where 0 is the best outcome.Possible pain change measured using NRS of 0–10, where 0 is the best outcome.Ratings of expectation, desire for relief, using NRS of 0–10, where 0 is the best outcome.Ratings of expectation, pain variability, using NRS of 0–10, where 0 is the best outcome.Activity levels are assessed using MPQ Short Version score of 0–45.Quality of life is assessed using questionnaire RAND-36 score of 0–100.Experience of the effect of the drug, assessed using questionnaire PGIC score of 1–7.Control of vitamin B_12_ is done by measuring cobalamin in plasma.Qualitative in-depth interviews will be conducted to capture women’s lived experiences of pain, health, suffering and well-being.

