#### Pressure algometry test

The pressure algometry test^32 33^ generates a mechanical pressure against specific points on the body: trapezius (shoulder), epicondyle (elbow), gluteal (outside the gluteal muscles) and medial knee (inside of the knee), which are all accepted in the diagnosis of fibromyalgia. Pressure algometry tests are measured in kilopascal. The trial manager interrupts the mechanical pressure when the participant expresses pain.

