### Statistical methods

The primary endpoint is tolerance time at cold pressor test and will be calculated on the difference between the two groups after 12 weeks and analysed by analysis of variance (ANOVA). Pain thresholds measured by pressure algometry test (Somedic) will be analysed using t-test and ANOVA, similar to the primary variable. Questionnaires (MPQ, RAND-36 and PGIC) will be analysed using Mann-Whitney tests. In cases of minor loss (less than 10%), a mixed model can be used as an alternative to t-test and ANOVA with repeated measurement. For variables with more than 10% loss, imputation of data will be used. Drop-out participants will be described in a specific analysis. Rejection analysis will be performed on the participants who interrupt the study prematurely.

Results will be reported for both intention-to-treat and per-protocol analyses. Intention-to-treat is defined as the participant is placed in the treatment group he or she had been randomised to. Per-protocol is defined as the participant is placed in the treatment group she de facto received and carried out without significant protocol deviations. The per-protocol results will be presented as sensitivity analyses. The participant may miss a maximum of two injections.

Self-reported ratings of desired and expected treatment outcome pretreatment and post treatment will be implemented in linear regression models to predict any of the outcome measures. Repeated ratings of desired treatment outcome, expected treatment outcome and pain variability will be calculated as each participant’s SD from the repeated ratings and implemented in a linear regression model to predict possible outcome measures.

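### Pressure algometry is listed as a value and as a change at four sites and compared at week 12 with no baseline covariate named; one baseline-adjusted ANCOVA would serve better, and the stated direction of benefit needs correcting

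*Protocol article*

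**What the plan says.** All references are to the protocol article.

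- **Aims and objectives** names one algometry quantity. The secondary objective asks whether mecobalamin, compared with placebo, "reduces pain intensity and pressure pain threshold".
- **Outcomes** lists algometry as two separate items: "Pain experience measured by a pressure algometry test performed on the shoulder, hip, knee and elbow" and "Possible pain change measured by a pressure algometry test performed on the shoulder, hip, knee and elbow".
- **Pressure algometry test** defines the four points as "trapezius (shoulder), epicondyle (elbow), gluteal (outside the gluteal muscles) and medial knee (inside of the knee"). The unit is kilopascal, and the pressure is stopped when the participant expresses pain. No combined score is given.
- **Measurements** places algometry at the first visit, before randomisation ("then stimulation tests (cold pressor test and pressure algometry")), and again at 12 weeks and 12 weeks after treatment ends.
- **Statistical methods** says the thresholds "will be analysed using t-test and ANOVA, similar to the primary variable". The primary variable, which this follows, "will be calculated on the difference between the two groups after 12 weeks and analysed by analysis of variance (ANOVA"). With less than 10% loss, "a mixed model can be used as an alternative to t-test and ANOVA with repeated measurement".

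**The concern.** The plan offers two versions of the outcome, four sites and two named tests for one objective, and does not say which of them answers it. Two analysts could both follow the text and report different algometry results.

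The stated comparison is between groups at week 12. A t-test takes no covariate and none is named for the ANOVA, so the baseline threshold, already collected, enters only through the change outcome or possibly a repeated-measures model. Neither is the efficient way to use it. With 20 per arm, precision is scarce.

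Separately, the objective describes benefit as a reduced threshold. Under the protocol's own definition, a reduced threshold means that pain is expressed at a lower pressure, which is greater sensitivity.

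**Working it through.** **1. The plan's own figure.** The only sample-size figure is for the primary outcome: difference 20 s, SD 20 s, two-sided 5%, power 80%. The normal approximation gives n = 2 × (1.960 + 0.842)² × (20/20)² = 15.7, so 16 per group, as stated. The exact noncentral t gives 78.1% power at 16, 80.7% at 17 and 86.9% at 20. No effect size, SD or power is given for algometry, so everything below rests on stated assumptions.

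**2. t-test and ANOVA.** For two groups at one visit, F = t². On one simulated data set with 20 per arm, both gave p = 0.0324. Read this way, the pair is redundant and adds no false positives.

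**3. False positives if each site is tested as value and as change.** Separate testing by site is an inference from the outcome list.

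- If tests were independent: four give 1 − 0.95⁴ = 18.5%; eight give 1 − 0.95⁸ = 33.7%.
- Tests on the same participants are correlated, so null trials were simulated: 10,000 per setting, 20 per arm, between-site correlation 0 to 0.9, between-visit correlation 0.3 to 0.8.

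| Set of tests at two-sided 5% | Chance of at least one false positive |
|---|---|
| Four site values at week 12 | about 9% to 19% |
| Four values plus four changes | about 16% to 34% |
| The same eight, between-site correlation 0.5 | about 27% to 29% |
| One ANCOVA on the four-site mean | 4.7% to 5.3% |

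**4. Precision.** Let r be the correlation between baseline and week-12 threshold, with equal variances at the two visits. Relative to the week-12 value alone, the variance is 1 − r² for ANCOVA and 2(1 − r) for change. Their ratio, change over ANCOVA, is 2/(1 + r), which exceeds 1 for every r below 1. Change is worse than the week-12 value alone when 2(1 − r) > 1, that is, when r < 0.5.

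Power is from the noncentral t with 20 per arm and an assumed true effect of 0.5 SD, replacing 0.5 by 0.5/√(variance ratio). The single degree of freedom spent on the covariate is ignored.

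| Assumed r | ANCOVA variance | Change variance | 20 per arm with ANCOVA acts like | Power: week 12 only | Power: change | Power: ANCOVA |
|---|---|---|---|---|---|---|
| 0.3 | 91% | 140% | 20/0.91 = 22 | 34% | 26% | 37% |
| 0.5 | 75% | 100% | 20/0.75 = 27 | 34% | 34% | 43% |
| 0.7 | 51% | 60% | 20/0.51 = 39 | 34% | 51% | 58% |

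Each row compares analyses of the same endpoint, so the gain is from baseline adjustment alone.

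**5. Direction.** The abstract's aim is a decrease in pain sensitivity. Algometry records the pressure at which pain is expressed. Less sensitivity therefore means a higher kilopascal value, and the objective's verb points the other way.

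**The case against.** The strongest reply is that a condensed article need not spell out covariates, the handling of sites or multiplicity for secondary outcomes; these may sit in the full protocol or the SAP, which are not shown. That stands for multiplicity: no finding is made that a correction is missing. It does not dispose of the rest, because the article does name a method for algometry, and that method can be improved at no cost in data.

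Several stronger readings are tempting, and the document does not support them.

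- **Sixteen p-values.** Four sites × two versions × two tests gives 16 on paper, but at one visit the t-test and one-way ANOVA coincide. The ANOVA would be a different test only if it means a repeated-measures model. The mixed-model sentence leaves that open, and baseline would then already be in the model.
- **Baseline is excluded.** The text is silent on covariates; it does not rule them out, and the change outcome uses baseline.
- **Half the precision is lost, or power would go from 34% to 63%.** Those figures set one unadjusted site against a baseline-adjusted mean of four sites, which mixes averaging with adjustment. With between-site and baseline correlations both assumed to be 0.6, averaging alone gives 45% and adjustment of one site alone gives 49%.
- **The objective cannot be answered without this.** That depends on the assumed 0.5 SD. At the one standardised effect the protocol uses, 20/20 = 1.0 for the primary outcome, an unadjusted test with 20 per arm has 87% power.

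It is also fair to say that the direction slip does not alter a two-sided test, and that the abstract makes the intention clear. It still leaves an objective that contradicts the measure.

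**Conclusion.** The point holds in a limited form. The stated algometry analysis leaves value and change unreconciled, names two tests that coincide at a single visit, and names no baseline covariate although the baseline is measured.

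The gain from one ANCOVA depends on r, which the document does not give. It is small at r = 0.3 and substantial at r = 0.7. The 16% to 34% false-positive range applies only if all four sites are tested separately both as value and as change, and it covers secondary tests only; the primary test keeps its 5% level. The direction of benefit in Aims and objectives is an inconsistency that needs no assumption.

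**What to change.** - **Statistical methods:** analyse the week-12 pressure pain threshold by one ANCOVA with arm and the baseline threshold as terms. This replaces the t-test/ANOVA pair and the separate test of change.
- **Outcomes:** preferably define the single algometry endpoint as the mean threshold in kilopascal over the four sites, with the baseline four-site mean as covariate. Merge the value and change items into it, and report the site estimates descriptively.
- **Aims and objectives:** reword so that benefit is a higher pressure pain threshold, in line with the abstract and the Pressure algometry test section.

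The cost is wording, settled before outcome data are analysed by arm; no new measurement is needed. The small downside of the four-site mean is that an effect confined to one site is diluted, though the descriptive site estimates would still show it.

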#### Patient Global Impression of Change

PGIC^35^ evaluates participants’ experience of the treatment, that is, the substance given. Participants tick the box that most closely describes the change that they are experiencing. The PGIC is completed by the participant after the injection treatment has been concluded at 12 weeks and at the follow-up 12 weeks later. PGIC is directly translated in its entirety from English by the research group.

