### Sample size

In order to obtain an adequate sample size, a power analysis was performed based on results from a previously published study^29^ in which women with fibromyalgia underwent the same stimulation procedure with the cold pressor test. Account is taken here of the SD shown and compensation for any placebo effects. Based on these results, the expected effect difference is estimated at 20 s with an SD of 20 s between the two groups after 12 weeks of treatment with mecobalamin (vitamin B_12_)/placebo. Using a two-sided t-test for two independent groups with a power of 80% and 5% significance level, it was calculated that each group would consist of 16 participants. In order to compensate for any loss, 20 participants per group are therefore included. The study continues until 40 participants have been included and have completed the study.

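### The MPQ and RAND-36 are compared by an unadjusted Mann-Whitney test although both have a baseline, and the imputation rule above 10% loss is not fitted to rank tests

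*Protocol article*

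**What the plan says.** The Statistical methods section of the protocol article fixes the test for all three instruments: "Questionnaires (MPQ, RAND-36 and PGIC) will be analysed using Mann-Whitney tests". It names no covariate for these tests.

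The same section gives two rules for missing data. Below 10% loss: "In cases of minor loss (less than 10%), a mixed model can be used as an alternative to t-test and ANOVA with repeated measurement". That option is tied to the t-test and ANOVA variables. Above 10%: "For variables with more than 10% loss, imputation of data will be used". The second rule applies to variables in general, so on a plain reading it includes the questionnaires.

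The sections on the short-form MPQ and RAND-36 say that both are completed on all three measurement occasions, so both have a baseline score. The PGIC has none: "The PGIC is completed by the participant after the injection treatment has been concluded at 12 weeks", and again 12 weeks later.

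On loss, the Sample size section says "In order to compensate for any loss, 20 participants per group are therefore included". It adds that the study runs on until 40 participants have been included and have completed it.

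**The concern.** Two features of the questionnaire analysis deserve a change.

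First, with 20 per arm, a baseline score correlated with the outcome is the cheapest source of precision available, and a plain Mann-Whitney test of the week-12 scores does not use it. The MPQ and RAND-36 carry the secondary objectives on activity level and quality of life, so the lost power falls on patient-reported results.

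Second, Mann-Whitney is named as a test, with no effect estimate beside it. Rubin's rules pool an estimate and its variance; they do not pool a p-value. An analyst following the article literally could fill in one data set and test it as if every score had been observed. Depending on how the values are filled in, that test would either reject a true null too often or lose power.

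**Working it through.** **1. The plan's own figure.** Inputs from Sample size: "the expected effect difference is estimated at 20 s with an SD of 20 s between the two groups"; "Using a two-sided t-test for two independent groups with a power of 80% and 5% significance level". The normal formula gives n = 2 × (1.960 + 0.842)² × (20/20)² = 15.7, so 16 per group, as stated. An exact t calculation gives 16.7, so 17. This differs by one patient and is not material here. No error rate or power is stated for the questionnaires.

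**2. Can loss exceed 10%?** Going from 16 to 20 per group allows for 4/20 = 20% loss. With 40 participants, five missing scores are 12.5%, which triggers the imputation rule; four are exactly 10%, which does not. Against this, recruiting until 40 have completed keeps loss low among completers. The intention-to-treat definition goes by randomised group, so dropouts can still count as loss. Loss above 10% is possible, not certain.

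**3. Cost of leaving out the baseline.** Assumptions not in the documents: effect 0.8 SD, baseline to week-12 correlation r = 0.5 or 0.7, normal scores, no loss, 20 per arm, two-sided 5%.

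- Adjustment multiplies the residual variance by 1 − r²: 0.75 at r = 0.5 and 0.51 at r = 0.7. An unadjusted comparison would need 20/0.75 = 26.7 or 20/0.51 = 39.2 per arm for the same precision.
- The standardised effect rises from 0.80 to 0.80/√0.75 = 0.92 and to 0.80/√0.51 = 1.12.

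| Analysis | Power, r = 0.5 | Power, r = 0.7 |
|---|---|---|
| Mann-Whitney, week-12 score (simulated) | 67% | 67% |
| Rank ANCOVA on baseline (simulated) | about 77-78% | about 89-90% |
| Linear model on baseline (simulated) | about 79-81% | about 92% |

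Under the null, rank ANCOVA rejected in 5.0% to 5.3% of 8,000 simulated trials.

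**4. Imputation followed by Mann-Whitney.** Assumptions: 20 per arm, 20% missing completely at random, r = 0.5; effect 0.8 SD where power is given.

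| Handling of missing scores | Type I error | Power |
|---|---|---|
| Observed scores only | 4-5% | 54-57% |
| Single, within arm: regression or hot deck | about 9-11% | not interpretable |
| Single, within arm: arm mean | 14-20% | not interpretable |
| Single, ignoring arm: hot deck | about 5% | 44-48% |
| Single, ignoring arm: overall mean | 3.5-5% | 52-56% |
| Multiple, Mann-Whitney index U/(nm) pooled by Rubin's rules | 2.8-4.2% | 51-56% |

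Ranges cover continuous and 7-point scores. At r = 0.8 the pooled index had 59.9% power against 56.5% on observed scores (continuous), and 54.4% against 53.0% (7-point).

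**5. The proposed model under loss.** Baseline-adjusted proportional odds at 20% loss, r = 0.5, 1,000 runs: with multiple imputation, type I error 5.2% and power 67.9%; on observed scores alone, 6.9% and 68.7%. The gain over Mann-Whitney comes from the baseline covariate; imputation adds no power.

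**The case against.** The strongest reply is that the article does not say how imputation will be done. Single or multiple, the imputation model and the pooling are details that a journal article leaves to the full protocol or the analysis plan, neither of which is shown. The inflated error rates appear only if single within-arm imputation is assumed, and the arm-mean figures come from the crudest choice. This stands: the missing detail is not a fault of the article, and the inflation is conditional.

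A reader might go further and infer that Mann-Whitney and imputation cannot be combined, so that the planned test must either give too many false positives or lose power. The documents do not support that. The index U/(nm) has an estimate and a variance and can be pooled. In the check it kept type I error below 5%, with power within about 4 points of the observed-score test.

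It can also be said that Mann-Whitney might be applied to change scores, since the article does not name the quantity tested. This helps only in part. The variance of a change, relative to that of the score, is 2(1 − r): 1.0 at r = 0.5, so no gain, and 0.6 at r = 0.7, against 0.75 and 0.51 with adjustment.

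Finally, these are secondary outcomes. The primary test and the sample size are untouched, and the 5% level is stated only for the primary calculation. That also stands, and limits the weight of the point.

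**Conclusion.** The point holds in two parts of unequal strength.

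The firmer part is the choice of test. For the MPQ and RAND-36 the article names a test without baseline adjustment although the baseline is collected. The cost is roughly 10 to 23 percentage points of power (67% against 77% to 90%). That rests on an assumed 0.8 SD effect and correlations of 0.5 to 0.7; a weaker correlation would shrink the gain.

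The second part is conditional. The rule for more than 10% loss covers the questionnaires but is paired with a test that offers nothing to pool directly. If it were carried out by single within-arm imputation, type I error would be about 9-11% at 20% loss. Nothing in the article commits the trial to that, and loss may stay below the threshold. For the PGIC, with no earlier PGIC score to impute from, imputation has little to add to the observed scores.

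This is a worthwhile, inexpensive improvement to secondary analyses. It does not threaten the primary result.

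**What to change.** In Statistical methods, replace the Mann-Whitney sentence with three statements.

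- Week-12 MPQ and RAND-36 scores are compared by a model with an arm coefficient, adjusted for the baseline score (proportional-odds regression or rank ANCOVA). If loss exceeds 10%, the coefficient is pooled over multiple imputations by Rubin's rules.
- The PGIC is analysed on observed scores, by Mann-Whitney or by proportional odds with arm only, without imputation.
- No test is run on a singly imputed data set.

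If the trial team prefers to keep Mann-Whitney throughout, pooling the Mann-Whitney index over multiple imputations removes the type I error problem but gives up the gain from the baseline.

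The cost is a few sentences, a model assumption to check (proportional odds, or linearity on the rank scale) and a little more analysis work. No new data or participants are needed. The change should be made before any unblinded analysis.

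### The primary week-12 test is not fixed in advance: the method depends on whether observed loss is below or above 10%, and below 10% the analyst may choose it

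*Protocol article*

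**What the plan says.** All of the following is in the protocol article.

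- **Primary analysis (Statistical methods).** Tolerance time "will be calculated on the difference between the two groups after 12 weeks and analysed by analysis of variance (ANOVA").
- **Pressure algometry thresholds (same section).** These "will be analysed using t-test and ANOVA, similar to the primary variable".
- **Loss below 10% (same section).** "In cases of minor loss (less than 10%), a mixed model can be used as an alternative to t-test and ANOVA with repeated measurement".
- **Loss above 10% (same section).** "For variables with more than 10% loss, imputation of data will be used".
- **Allowance for loss (Sample size).** The calculation gives 16 per group, and "In order to compensate for any loss, 20 participants per group are therefore included". The same section adds that the study runs until 40 women have completed it.
- **Analysis sets (Statistical methods).** Both intention-to-treat and per-protocol results are reported, with per-protocol as the sensitivity analysis.

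**The concern.** A primary analysis should be settled before anyone sees the data. Here two things are left to the data or to the analyst.

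1. Below 10% loss the word *can* permits either of two analyses, and nothing says which is primary if they disagree.
2. The 10% threshold decides whether the analysis rests on observed or imputed data. It is applied to each variable separately, so two outcomes in the same trial may be handled differently.

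The direction of the rule is also odd. A likelihood-based mixed model uses partly observed participants under a missing-at-random assumption, and that gains importance as loss grows. The text offers it only where loss is small.

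At stake is the 5% error rate of the one primary test in a trial of 40 women, and how credible the result would be if the permitted analyses fell on opposite sides of 5%.

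**Working it through.** **1. The plan's own figure.** From Sample size: difference 20 s, SD 20 s, two-sided 5%, power 80%.

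n per group = 2 × (1.960 + 0.842)² × (20/20)² = 15.7, rounded up to 16. This matches the stated 16. An exact t calculation gives 78.1% power at 16 and 80.7% at 17, a rounding-level difference that does not bear on this point. The margin from 16 to 20 per group is (20 − 16)/20 = 20%.

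**2. Does the rule reach the primary endpoint?** The under-10% sentence governs t-test and ANOVA. The primary is an ANOVA, and the algometry analysis by t-test and ANOVA is described as similar to it. So the rule reaches the primary by clear implication, though not by name. The over-10% sentence covers every variable.

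**3. Which branch applies?** With 40 randomised, 10% is 4/40.

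| Missing at week 12 | Loss | What the text says |
|---|---|---|
| 0 to 3 | 0% to 7.5% | t-test/ANOVA, or a mixed model at the analyst's choice |
| 4 | exactly 10% | no rule |
| 5 or more | 12.5% or more | imputation required |

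The denominator is not settled, because recruitment continues until 40 complete. With 40 completers, 4 lost is 4/44 = 9.1% and 5 lost is 5/45 = 11.1%. One further woman without a week-12 value then moves the primary analysis from one branch to the other. On that denominator no whole number of losses gives exactly 10%.

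**4. How often would each branch apply?** The documents forecast no loss rate, so a range is assumed (binomial, 40 randomised).

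| Assumed true loss | Fewer than 4 | Exactly 4 | More than 4 |
|---|---|---|---|
| 5% | 86% | 9% | 5% |
| 10% | 42% | 21% | 37% |
| 15% | 13% | 13% | 74% |
| 20% | 3% | 5% | 92% |

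Either branch is possible, and the table does not say which is likely.

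**5. What could the open choice cost?** Simulation with no treatment effect: 37 of 40 observed (19 and 18 per arm), normal data, baseline-to-week-12 correlation assumed, 200,000 trials per row. The baseline-adjusted model stands in for a mixed model that uses baseline. The last column counts a trial as significant if either analysis gives p < 0.05.

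| Correlation | Week-12 t-test alone | Baseline-adjusted alone | Either |
|---|---|---|---|
| 0.3 | 5.0% | 5.0% | 6.4% |
| 0.5 | 4.9% | 4.9% | 7.2% |
| 0.7 | 5.0% | 5.0% | 8.2% |

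Each analysis is valid alone. The excess comes only from choosing between them after seeing the results.

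**The case against.** The strongest reply is that a threshold on the amount of loss, fixed in advance, does not by itself select on the treatment effect, and that imputation can be followed by the stated ANOVA. That is right. The threshold makes the method depend on the data, but the error inflation comes from the open choice below it. The simulated rates also depend on how the mixed model would use baseline, which the text does not specify, so they are illustrative.

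A reader might infer four stronger things that the documents do not support.

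- **That imputation here will inflate type I error.** This would follow from, for example, single mean imputation. The text names no method, and a condensed article may leave that to the analysis plan. Valid multiple imputation would not have this effect.
- **That the imputation branch is the likely one, because the sample size allows 20%.** The 20% is a margin against any loss and not a forecast, and recruitment continues until 40 have completed.
- **That women who miss only week 24 are dropped from the primary test.** The primary is a week-12 comparison, so a missed week-24 visit does not remove anyone from it.
- **That a mixed model would recover women lost early.** According to Measurements, the first post-baseline cold pressor test is at week 12. A woman lost before then has no post-baseline value and adds almost nothing to such a model.

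The text also does not forbid a mixed model above 10%; it simply does not mention one there. What remains is a stated rule, and not a missing detail: an analysis plan that followed it would inherit a discretionary primary analysis.

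**Conclusion.** The point holds in this form: the primary week-12 test is not fixed in advance. Below 10% loss the analyst has a choice without a criterion, above 10% imputation is required variable by variable, and exactly 10% is covered by neither rule. The exact-10% gap is real for the primary endpoint if the denominator is 40 randomised women.

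The possible cost is a type I error of about 6% to 8% in place of 5%. This assumes that the choice lies between an unadjusted and a baseline-adjusted week-12 analysis, that the better result is reported, and that the baseline correlation is 0.3 to 0.7. No stated figure is wrong, and 16 and 20 per group stand.

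**What to change.** Delete the 10% switch and the word *can*. Name one primary model for any amount of loss that tests the week-12 group difference in tolerance time with baseline tolerance time as a covariate. Two forms are suitable, and one should be written down:

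- ANCOVA at week 12; or
- a mixed model for weeks 12 and 24 with treatment, visit, treatment-by-visit, baseline and baseline-by-visit, testing the week-12 contrast.

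With an unstructured covariance, and if no woman has a week-24 value without a week-12 value, the two give the same week-12 estimate.

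Keep all randomised women in their assigned group. Add multiple imputation as a sensitivity analysis, including a delta-adjusted not-at-random version, so that women with no post-baseline value are also covered.

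Cost: protocol or analysis-plan wording and slightly more programming. No extra participants, visits or data are needed. It should be settled before any unblinded analysis.
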